#### Safety assessment index

All informations including vital signs, general medical examinations, laboratory test results, and adverse events will be recorded for the safety assessment.

### Procedures

#### Recruitment

Subjects will be recruited through two routes. Patients who visit the trial hospitals and meet the criteria will be recommended by a physician in charge. Those who see the trial poster on bulletin boards will visit the trial site voluntarily.

#### Study schedule & test items per visit

The detailed items which will be measured at every visit are described in Table 4.

**Table 4 T4:** Study schedule. A brief study schedule at every visit

	Screening* Visit 1	Baseline Visit 2	Visit 3	Visit 4	Follow up (Visit 5)
	
	D-21 ~D-1	D0 Week 0	D21 Week 3	D42 Week 6	D56 Week 8
Informed consent form	●				

Demographic information taking ^1^	●				

Medical history taking	●				

Finger-prick blood glucose testing	●				

QSCC II ^2^	●				

Inclusion/exclusion criteria check	●				

Physical examination ^3^	●	●	●	●	

Vital sign measurement ^4^	●	●	●	●	

Laboratory test ^5^	●	●	●	●	

VAS ^6^	●	●	●	●	

Electrocardiogram(ECG)	●			●	

Concomitant drugs check	●	●	●	●	

Treating physician examination ^7^	●	●	●	●	

Adverse event monitoring			●	●	●

Compliance checking			●		

Study drug distribution		●	●		

Smoking, drinking, coffee taking status ^8^	●				

Diet, physical exercise Counseling ^8^		●	●		

●: Item need to be carried out during the visit.

* required to fast from 10 p.m. the day before the test prior to the blood sample collection.

^1 ^sex, date of birth, age, contact address and phone number.

^2 ^Questionnaire for the Sasang Constitution Classification II

^3 ^body weight(kg), height(cm), waist circumference(cm), hip circumference(cm).

^4 ^blood pressure(mmHg), pulse(/min), body temperature(°C).

^5 ^blood test (WBC, RBC, hemoglobin(HGB), hematocrit(HCT), platelet count(PLT), AST, ALT, γ-GTP, total bilirubin, albumin, total protein, total cholesterol, triglyceride, HDL cholesterol, BUN, creatinine, glucose(fasting), 2h-OGTT glucose, HbA1c, fructosamine, insulin(fasting)), urine test.

^6 ^visual analogue scale: polydipsia, polyuria, polyphasia, fatigue.

^7 ^includes present illness, past history taking.

^8 ^risk factors such as smoking, alcohol drinking, severe exercise and other drug intake will be managed strictly.

### Measurement tools

#### Visual analogue scale (VAS)

A 10 cm VAS (ranging from 0 cm as no symptom to 10 cm as the maximum symptom) will be used to assess diabetic symptoms (polydipsia, polyuria, polyphasia, and fatigue) improvement during treatment term.

#### Anthropometric measurements

The items will be measured with a standard operating procedure (SOP) by the well-trained physicians. All participants will be measured in light garments (estimated approximately 0.5 kg) and bare feet. The waist circumference (WC: recorded to the nearest 0.1 cm) will be taken 2.5 cm above the umbilicus at the upright position. The hip circumference (HC: to the nearest 0.1 cm) will be measured at the horizontal level of the widest part of the hip.

#### Questionnaire for the Sasang Constitution Classification II (QSCC II)

A QSCC II is a questionnaire which categorizes a person into four types of constitution by its characteristics, in traditional Korean medicine. We will use this questionnaire to classify Korean pre-diabetes and diabetes (not insulin requiring stage) patients. Also we will apply this questionnaire to evaluate the association between the pre-diabetes susceptibility and the patient's constitution. Moreover, we will use this to assess which constitution responds well to PURIAM110 [28].

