### Population

The Korea Food & Drug Administration (KFDA)'s rule recommends including not only healthy group but also a sub-health condition population when conducting dietary supplement trials. Therefore, we included pre-diabetes status, and diabetes mellitus non-insulin dependent stage Korean adults, aged 18 to 65. The detail inclusion and exclusion criteria are described in Table 1 and Table 2.

**Table 1 T1:** Inclusion criteria. Inclusion criteria of the PURIAM110 trial

Inclusion criteria	
1.	Both gender between the ages of 18-69 years, eligible for study through screening test prior to the enrolment.
2.	Able and willing to perform the study protocol and participate throughout the entire trial period(Screening, baseline, 3, 6 weeks, follow up(if needed)).
3.	Participants who understood the risks and benefits of the study and signed a written informed consent.
4.	Among individuals not under diabetes mellitus treatment, whose random glucose concentration is 110~250 mg/dL measured with Accu-Chek^®^(Roche, Germany) glucometer within 3 weeks prior to participation.
4.1.	fasting plasma glucose concentration is 100-190 mg/dL or
4.2.	2- hour plasma glucose concentration* is 130-250 mg/dL( * venous plasma glucose 2-hour after ingestion of 75 g oral glucose load; DIASOL-S LIQ. [Glucose] Taejoon Pharm.)

**Table 2 T2:** Exclusion criteria. Exclusion criteria of the PURIAM110 trial

Exclusion criteria	
1.	Presently using other blood glucose level controlling agents.
2.	History of allergy to the herbal products (bitter oranges and Mulberry leaves) or allergic diseases such as asthma.
3.	Medication (within the last 1 month or during the study) which would affect the study results.
4.	Daily intake of alcoholic beverages.
5.	Smokers consuming more than 1 pack/day.
6.	Presently having acute diseases or other untreated illness requiring treatment.
7.	Impaired hepatic or renal functions.
8.	Pregnant, breast feeding status or female of reproductive age, not using proper contraception.
9.	Participant in other clinical trials or a blood donor, within the past 1 month.
10.	History of severe disease or any condition, in the investigator's opinion, that would endanger the individual's safety or affect the study result.
11.	Patients diagnosed as type I and type II diabetes mellitus(insulin requiring stage).

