### Sample size

We had difficulties in determining adequate sample size, as preliminary studies were insufficient. So we adopted a pilot study design.

Two points had to be considered in deciding the sample size. One was the special condition of herb-derived dietary supplements regulatory law in Korea, and another was limited research fund. Since herbs have historical efficacy and safety profile in Korea, KFDA regulates dietary supplements under a different rule, compared to conventional drugs. In other words, as the efficacy and safety of herbal products have been clinically validated for a long time, the regulatory authorities have lightened restrictions, such as minimizing sample size. We have planned the dietary supplement study according to this KFDA rule. The KFDA rule prescribes that when designing a dietary supplements trial, the sample size has to be a minimum 30 per group. Therefore we first fixed the number of the subjects in the treatment group as 30.

As the research funding was restricted, we plan to allocate 15 individuals for the placebo group. When sample size is inevitably restricted, it is considered to be more ethical by the KFDA to set more subjects in the test group than in the control group. In conclusion, a total of 45 subjects will be recruited in this pilot study.

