### Randomization

The study subjects will be randomly assigned to either PURIAM110 or placebo group at a ratio of 2:1, according to the 'random number table' generated by SAS software package (SAS institute, Inc, Carey, NC, USA, version 8.2).

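### The link between constitution type and susceptibility to pre-diabetes cannot be estimated from the enrolled sample; response by type can be estimated, but only very imprecisely

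*Protocol article*

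**What the plan says.** The QSCC II section of the protocol article describes a questionnaire that "categorizes a person into four types of constitution by its characteristics". It gives three uses: to classify the enrolled patients by type, to "evaluate the association between the pre-diabetes susceptibility and the patient's constitution", and a third, put as "we will use this to assess which constitution responds well to PURIAM110".

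On who is enrolled, the Population section says "we included pre-diabetes status, and diabetes mellitus non-insulin dependent stage Korean adults". Table 1 sets the glucose entry conditions: a random glucose of 110-250 mg/dL, with either a fasting value of 100-190 mg/dL or a 2-hour value of 130-250 mg/dL. The Study groups section lists two arms, PURIAM110 and placebo.

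On numbers, the Sample size section says "Therefore we first fixed the number of the subjects in the treatment group as 30" and "we plan to allocate 15 individuals for the placebo group", so that "a total of 45 subjects will be recruited in this pilot study". Subjects are "randomly assigned to either PURIAM110 or placebo group at a ratio of 2:1"; no stratification by constitution is stated.

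Table 4 places the QSCC II at the screening visit only. The Efficacy analysis section describes no analysis by constitution.

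**The concern.** To link constitution with susceptibility to a condition, the frequency of each type must be compared between people with and without that condition, or with a known distribution in a suitable reference population. The article enrols only the affected and names no reference. Followed as written, the aim would turn a table of type frequencies among patients into a statement about risk that the data do not support.

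The response aim is a different case. It asks a question that the randomized arms can address, but 45 subjects over four types leave very few in each. The article does not say that the answer will be only exploratory.

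**Working it through.** **1. Susceptibility: the sections side by side.** No arithmetic applies.
- The QSCC II section seeks an association between type and susceptibility to pre-diabetes.
- Population and Table 1 admit only people within the stated glucose ranges, whom the article treats as having pre-diabetes or diabetes not requiring insulin.
- Study groups has two arms, both drawn from these people.
- Unaffected subjects among those enrolled: 0. The proportion affected is 100% in every type, so the enrolled data hold no contrast from which to form a risk ratio or odds ratio. Enrolling more people under the same criteria would not create one.
- Contrasting pre-diabetes with diabetes within the sample would address stage of disease, not susceptibility to pre-diabetes.
- The section already lists plain classification of patients as a separate use, so the susceptibility aim is meant as more than description.

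**2. Response by type: precision.**

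The plan's own figure first: 30 + 15 = 45, and 45 × 2/3 = 30 with 45 × 1/3 = 15, which agrees with the 2:1 ratio. The size comes from a regulatory minimum and funding, so there is no power calculation to reproduce.

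Inputs from the article: 30 active, 15 placebo, four types. Assumption made here: equally common types. The article gives no type frequencies and no outcome SD, so results are in SD units.

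- Per type: 30/4 = 7.5 active, 15/4 = 3.75 placebo.
- SE of the treatment difference within a type: sqrt(1/7.5 + 1/3.75) = sqrt(0.400) = 0.63 SD.
- SE for the whole trial: sqrt(1/30 + 1/15) = sqrt(0.100) = 0.32 SD, half as large.
- 95% half-width using that type's data alone (7.5 + 3.75 − 2 = 9.25 df): 2.25 × 0.632 = 1.42 SD. With a variance pooled over all eight type-by-arm cells (45 − 8 = 37 df): 2.03 × 0.632 = 1.28 SD. For the whole trial it is 0.64 SD.
- SE of the difference in treatment effect between two types: sqrt(2 × 0.400) = 0.89 SD. Power at two-sided 5% (normal approximation) is 8%, 14% and 20% for true differences of 0.5, 0.8 and 1.0 SD.

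**3. Sensitivity to the equal-frequency assumption.** Take an assumed split of 45/30/20/5%.

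| Type share | Expected active | Expected placebo | SE (SD units) |
|---|---|---|---|
| 45% | 13.5 | 6.75 | 0.47 |
| 30% | 9 | 4.5 | 0.58 |
| 20% | 6 | 3 | 0.71 |
| 5% | 1.5 | 0.75 | 1.41 (notional) |

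The commonest types gain and the rarer ones lose. By simulation, at least one type has 0 or 1 placebo subject in about 31% of trials with equal frequencies and about 88% with this split. At least one type has no placebo subject in about 5% and 49% respectively.

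**The case against.** Four objections carry weight.

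**Screened-out people might supply a comparator.** The QSCC II is given at screening, in the same visit as the glucose tests, so some people who fail the glucose criteria could have both a type and a glucose result. An external distribution of types could also serve in principle. This stands to the extent that a reader should not infer that susceptibility is beyond any study of any kind: the limit applies to the enrolled sample. It does not rescue the aim, because the article plans no such comparison and names no reference, and those screened out are a selected group, some of them excluded for other reasons in Table 2.

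**The response aim is weak, not unanswerable.** This stands. Treatment is randomized, so any type with subjects in both arms yields an estimate. A reader might infer that the design cannot address response at all, but the article supports only the charge of low precision.

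**No faulty subgroup test is planned.** This also stands. One might infer that separate significance tests will be run in each type and a responding type picked by chance. The Efficacy analysis section plans no such tests; its before-after tests in each group read most naturally as referring to the two arms. The choice of test for an ancillary subgroup question may be left to an analysis plan that is not shown, so its absence is not held against the article.

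**The large trial is not put at risk.** A reader might fear that a mistaken type finding would shape the later RCT. The Discussion names sample size and primary endpoint as the two matters the pilot must decide, and constitution is neither. It is also absent from the objectives, the hypothesis and the outcomes.

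**Conclusion.** The point on susceptibility holds and needs no numerical assumption: with no unaffected subjects enrolled and no reference named, the association cannot be estimated from the enrolled sample. An analysis plan could specify a test, but it could not produce a contrast among enrolled subjects who are all affected.

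The point on response is secondary and one of degree. With four equal types, each type's effect has an SE of about 0.63 SD and a 95% CI of about ±1.4 SD (about ±1.3 SD with a pooled variance). Differences between types of up to 1 SD would be detected at most about one time in five. These figures rest on the equal split, which is assumed here; rarer types would fare worse and the commonest somewhat better.

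Both uses are ancillary. Neither affects the PURIAM110-placebo comparison in the whole sample. The wording should be changed, but nothing in the design has to be.

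**What to change.** - Replace the susceptibility aim with a description of the distribution of constitution types among enrolled subjects (counts and percentages), with no association or risk claim.
- For response by type, report each type's PURIAM110-placebo difference with its 95% CI and the number of subjects in each arm.
- Rest any claim that types differ in response on a treatment-by-constitution term in the between-arm model.
- Label the response results hypothesis-generating.

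The cost is a rewritten sentence or two and one model term. No extra subjects, visits or measurements are needed. The sponsor gives up one ancillary claim that the enrolled sample could not support.

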### Compliance calculation

The researchers should provide the investigational drug to the randomized participants in time and explain medication to them. Compliance of subjects will be evaluated by the below formula. Subjects are asked to return remaining drugs.

Compliance(%) = [(distributed drugs-remained drugs)/distributed drugs] ×100

### Statistical analyses

#### Efficacy analysis

All analyses in this study will be based on both intention-to-treat (ITT) and per protocol (PP) method. The ITT method will include all randomized subjects who made at least one next visit. The participants who have completed the 6-week treatment without major protocol violations and kept compliance rate over 80% will be analyzed by the pp (per protocol) method. The continuous variables will be summarized as mean±SD (standard deviation) and the categorical variables will be described in frequency and percent. For the primary and secondary outcome variables, the mean differences between before (visit 2; baseline) and after the treatment (visit 4) values will be compared using the paired t-test or Wilcoxon test, in each group. The baseline characteristics will be compared by either the Student t-test for the continuous variables or χ^2^-test for the categorical data (alternatively, Fisher's exact test will be used if the expected value is less than 5 or McNemar's test for non-normal distribution data). The efficacy of PURIAM110 will be assessed by using the independent t-test (when normality assumption is satisfied, alternatively Mann-Whitney test will be used). All analyses will be based on a two-sided test at a 5% significance level. With values of p < 0.05 will be considered statistically significant. SPSS for windows version 12.0 (SPSS Inc., Chicago, Illinois) will be used for analyses. For missing values, 'Last Observation Carried Forward (LOCF)' method will be applied.

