#### Hypothesis

We hypothesize that glucose concentration of pre-diabetes and diabetes mellitus who are treated with PURIAM110 will be lower than that of the control group. Also, we expect that other diabetes related parameters (total cholesterol, triglyceride, and LDL cholesterol) to be improved and the symptoms to be normalized in the treatment group.

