1.5. Fasting insulin

1.6. Total cholesterol

1.7. Triglyceride

1.8. Low density lipoprotein (LDL) cholesterol

##### Secondary outcome index

1. Diabetes symptoms*

1.1. polydipsia

1.2. polyuria(frequent urination)

1.3. polyphasia

1.4. fatigue

2. Other clinically significant parameters**

3. Anthropometric parameters:

3.1. body weight(kg)***

3.2. waist circumference(WC, cm)

3.3. hip circumference(HC, cm)

The primary and secondary outcomes will be measured at the 0th day (visit2; baseline), the 21th day (visit3; 3rd week), and the 42nd day (visit4; 6th week) during the treating period. And, when necessary, the outcomes will be assessed at the 56th day (follow-up). The changes between the 0th day (visit2; baseline) and the 42nd day (visit4; 6th week) measurements will be analyzed for the primary outcome indexes. For the secondary outcomes, a visual analogue scale (VAS) will be used to detect the improvement of diabetic symptoms (*). When the scale has improved more than two grades or a patient has recovered completely from these symptoms, it will be evaluated as 'effective'. For other categories (**), we will assess whether these parameters have normalized or not. Measured weight minus 0.5 kg (participant's garment weight) will be recorded as the subject's true weight (***).

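### The between-arm efficacy test is valid but omits baseline adjustment, the within-arm tests are not limited to description, and McNemar's test is misassigned in the baseline comparison

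*Protocol article*

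**What the plan says.** All three elements are in the protocol article under Statistical analyses, Efficacy analysis.

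- **Between arms.** "The efficacy of PURIAM110 will be assessed by using the independent t-test", or by Mann-Whitney if normality is not satisfied. No covariate is named. The sentence does not say which quantity is tested. The Outcomes section supplies it for the primary outcomes only: "The changes between the 0th day (visit2; baseline) and the 42nd day (visit4; 6th week) measurements will be analyzed for the primary outcome indexes".
- **Within arms.** For primary and secondary outcomes, visit 2 and visit 4 values "will be compared using the paired t-test or Wilcoxon test, in each group". The section adds: "All analyses will be based on a two-sided test at a 5% significance level". Nothing marks the within-arm tests as descriptive.
- **Baseline comparison.** Arms are compared by Student's t-test, chi-squared test or Fisher's exact test, or by "McNemar's test for non-normal distribution data".

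The context is as follows. The Hypothesis section is comparative: glucose under PURIAM110 "will be lower than that of the control group". Table 4 schedules "Diet, physical exercise Counseling" at visits 2 and 3, with no split by arm. Table 1 requires raised glucose at entry. Under Sample size, "we first fixed the number of the subjects in the treatment group as 30", and 15 are allocated to placebo.

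**The concern.** The baseline value of every outcome is measured at visit 2, yet the efficacy test uses it at most through subtraction. With funding holding the trial at 45 subjects, precision that could be had from existing data is given up.

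The within-arm tests raise a different problem. Both arms can improve through counselling, or through regression to the mean after selection on raised glucose, with no supplement effect. A paired test in one arm cannot tell these sources apart. Because the active arm is twice the size of the placebo arm, the same improvement reaches significance more often there. A result that is significant on PURIAM110 and not on placebo invites an efficacy reading that it does not support. The Discussion section says the primary outcome of the later trial will be chosen among the glucose and lipid parameters from this study's results, without saying which results. Such a pattern could therefore steer that choice.

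The McNemar rule cannot be carried out as written. The test is for paired binary data, whereas this comparison is of two independent groups on a non-normal variable.

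**Working it through.** **Inputs from the document.** 30 on PURIAM110 and 15 on placebo; two-sided 5% level; change from day 0 to day 42 for the primary outcomes. The stated total reproduces: 30 + 15 = 45, and 30/15 = 2 agrees with the 2:1 ratio. There is no power figure to reproduce; the size rests on a regulatory minimum and on funding.

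**Assumed, because the document gives no figure.** Baseline-outcome correlation r from 0.3 to 0.9; equal standard deviation s at both visits; a supplement effect of 0.5 s for the power illustration; a common true change of 0 to 1 SD of change for the within-arm illustration.

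**1. Change score against ANCOVA.** Var(change) = 2(1 − r)s². Residual variance of ANCOVA = (1 − r²)s² = (1 − r)(1 + r)s². The ratio is (1 + r)/2. Power is from the noncentral t with standard error factor √(1/30 + 1/15), on 43 degrees of freedom for change and 42 for ANCOVA.

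| r | Variance ratio | Reduction | Power, change | Power, ANCOVA |
|---|---|---|---|---|
| 0.3 | 0.65 | 35% | 25.7% | 36.7% |
| 0.5 | 0.75 | 25% | 34.0% | 43.0% |
| 0.7 | 0.85 | 15% | 51.4% | 58.1% |
| 0.8 | 0.90 | 10% | 68.6% | 73.1% |
| 0.9 | 0.95 | 5% | 93.3% | 94.3% |

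At r = 0.5, ANCOVA matches the precision of 45 subjects on change scores with 45 × 0.75 ≈ 34 subjects. At r = 0.9 it needs 45 × 0.95 ≈ 43.

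**2. Within-arm tests when both arms truly change by the same amount.** For a common change of d SDs of change, P(significant) in an arm of n comes from the noncentral t with noncentrality d√n and n − 1 degrees of freedom. Call it P30 and P15. The arms are independent, so significance on PURIAM110 only has probability P30 × (1 − P15), and on placebo only P15 × (1 − P30).

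| d | P30 | P15 | PURIAM110 only | Placebo only |
|---|---|---|---|---|
| 0 | 5.0% | 5.0% | 4.8% | 4.8% |
| 0.2 | 18.5% | 11.2% | 16.5% | 9.1% |
| 0.3 | 35.5% | 19.2% | 28.7% | 12.3% |
| 0.5 | 75.4% | 43.8% | 42.4% | 10.8% |
| 0.8 | 98.8% | 82.1% | 17.7% | 0.9% |
| 1.0 | 100.0% | 94.9% | 5.1% | 0.0% |

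For d = 0.5: 0.754 × (1 − 0.438) = 0.424. The PURIAM110-only figure peaks near d = 0.5 and falls on both sides.

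**3. The between-arm test in the same no-effect case.** Simulating 40,000 trials with a common change of 0.5 SD (r = 0.7), the independent t-test on change rejected in 5.1%. The shared change cancels.

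**4. McNemar's test.** It needs two binary readings on the same subject. The baseline comparison has one reading per subject in two separate groups, so there are no pairs to form.

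**The case against.** The strongest reply is that the plan gives efficacy to one test, a between-arm comparison that agrees with the hypothesis and holds its 5% level. That stands. A reader might infer that counselling can pass for a supplement effect in the efficacy test. It cannot, because an effect common to both arms cancels there. Only the within-arm tests are exposed, and the plan does not assign efficacy to them. But neither does it restrict them, and the 5% criterion is applied to all analyses.

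A reader might also say that the baseline is wasted. It is not: a change score is a legitimate, unbiased comparison in a randomised trial that uses the baseline inefficiently. The gain from ANCOVA depends on a correlation the document does not give, and at r = 0.9 it is about one power point.

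The 42% figure should not be read as the expected rate. It is close to the maximum over the assumed range, and nothing in the document supports a common change of 0.5 SD over any other.

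The McNemar slip is confined to the baseline comparison. For efficacy, the same section names Mann-Whitney for non-normal data.

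Adjusting for hospital, fixing log transformations in advance, and deleting the within-arm or baseline tests outright are matters of preference, and the point does not depend on them. Choosing between t-test and Mann-Whitney by distribution is conventional. A condensed article may leave model detail to an analysis plan, but the tests discussed here are ones this article states.

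**Conclusion.** The point holds at should-fix level, in three parts.

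- The unadjusted between-arm test is valid but less precise than ANCOVA for every r below 1. The variance reduction runs from 35% at r = 0.3 to 5% at r = 0.9, assuming equal variances at the two visits.
- The within-arm tests cannot separate the supplement from counselling or regression to the mean. Under an equal true change in both arms, unequal arm sizes produce significance on PURIAM110 only in about 5% to 42% of trials over an assumed common change of 0 to 1 SD. The remedy is a limit on their interpretation, since the efficacy test itself is unaffected.
- McNemar's test is wrong for the purpose named. This needs no assumption, and it touches no efficacy result.

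None of this invalidates the planned efficacy comparison.

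**What to change.** In the Efficacy analysis section:

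1. For each continuous outcome, make the efficacy analysis a between-arm ANCOVA of the day-42 value on treatment and baseline value, reporting the adjusted difference with its 95% confidence interval.
2. State that within-arm changes are descriptive only and support neither a conclusion on efficacy nor the choice of endpoint for the later trial.
3. Replace McNemar's test with Mann-Whitney for non-normal continuous baseline variables.

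The cost is one degree of freedom (43 to 42) and a change of wording. No new data are needed, since the baseline values are already collected at visit 2. The baseline-outcome correlation estimated in this pilot would also serve the sample-size calculation for the larger trial, which the protocol lists as its secondary objective.

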**Discussion:**

The present protocol will confirm the efficacy and safety of PURIAM110 for pre-diabetes, suggesting more basic knowledge to conduct further randomized controlled trials (RCT). In addition, PURIAM110 can be an alternative dietary supplemental remedy for diabetes patients.

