### Outcomes

#### Efficacy assessment index

##### Primary outcome index

1. Biochemical parameters:

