1.1. HbA1c

1.2. Fructosamine

1.3. Fasting glucose

1.4. 2-h OGTT glucose

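### Eight unranked primary outcomes are each tested at an unadjusted 5% in both ITT and PP, so the stated level does not describe the risk of a chance finding if any one significant outcome is read as efficacy

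*Protocol article*

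**What the plan says.** All places are in the protocol article.

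- **Outcomes.** Under "Primary outcome index" the list runs from HbA1c, fructosamine, fasting glucose and "1.4. 2-h OGTT glucose" to fasting insulin, total cholesterol, triglyceride and finally "1.8. Low density lipoprotein (LDL) cholesterol". That makes eight outcomes with no order of importance. All share the same contrast, the change from day 0 to day 42.
- **Efficacy analysis.** The groups are compared by an independent t-test, or Mann-Whitney if normality fails. The level is "All analyses will be based on a two-sided test at a 5% significance level", followed by "With values of p < 0.05 will be considered statistically significant". On analysis sets: "All analyses in this study will be based on both intention-to-treat (ITT) and per protocol (PP) method". Neither set is named as leading. The section contains no adjustment, no testing order and no rule on how many outcomes must succeed.
- **Objectives.** Assessing efficacy and safety is the primary objective. Estimating the sample size and the primary endpoint for a later large RCT is secondary.
- **Hypothesis.** It opens with glucose, "We hypothesize that glucose concentration of pre-diabetes and diabetes mellitus who are treated with PURIAM110 will be lower", and then adds that total cholesterol, triglyceride and LDL cholesterol are also expected to improve.
- **Abstract, Discussion paragraph.** "The present protocol will confirm the efficacy and safety of PURIAM110 for pre-diabetes". The sentence goes on to say that this will inform further RCTs.
- **Main Discussion.** A confirmative conclusion needs a full-scale RCT, and the primary outcome of that trial will be chosen among the glucose and lipid parameters from this study's results.

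**The concern.** A 5% level describes the chance of a false positive for one test. The article applies it separately to eight co-equal primary outcomes, repeats the tests in a second analysis set, and then speaks of confirming efficacy. A reader of the results would have no pre-stated basis for telling one significant parameter out of eight from a chance finding.

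This is more than a detail left to an analysis plan. Naming eight equal primaries is a protocol-level choice, and the article does state a decision rule: an unadjusted 5% throughout.

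The pilot's own aim is also affected. If the later trial's endpoint is the one that looks best among eight in 45 subjects, its observed effect will tend to be too large, and that effect would feed the next sample-size calculation.

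**Working it through.** **Inputs from the article**
- Outcomes: k = 8 (list items 1.1 to 1.8).
- Level per test: two-sided 0.05, unadjusted.
- Group sizes: 30 PURIAM110 and 15 placebo (Sample size), which agrees with the 2:1 ratio and the total of 45.
- Test: independent t-test, with 30 + 15 − 2 = 43 degrees of freedom.

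**Assumptions, because the article gives no figure**
- Correlation among the eight outcomes: a common value from 0 to 0.9.
- Reading rule: any one significant outcome is taken as efficacy.
- Direction: for the one-directional figures, lower is counted as favourable for all eight.

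**Stated figure.** The 5% is a chosen level, so there is nothing to derive. For one test it is exact: 1 − 0.95 = 5.0%, of which 2.5% lies in PURIAM110's favour.

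**Eight independent tests.** 1 − 0.95^8 = 1 − 0.663 = 33.7%. This is the value under independence and not the expected rate, since related metabolic measures will correlate.

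**Eight correlated tests.** Simulation with no true effect: equally correlated normal outcomes, 30 vs 15, pooled t-test, 200,000 runs per row. Separate runs of 40,000 agreed to within about one percentage point.

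| Assumed correlation | At least one p < 0.05, either direction | At least one p < 0.05 favouring PURIAM110 |
|---|---|---|
| 0 | 34% | 18% |
| 0.3 | 30% | 15% |
| 0.5 | 25% | 13% |
| 0.7 | 19% | 10% |
| 0.9 | 12% | 6% |
| One test only | 5% | 2.5% |

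A block pattern (0.7 among the five glycaemic measures, 0.5 among the three lipids, 0.2 between the blocks; 40,000 runs) gives 25% and 13%.

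For correlations of 0.3 to 0.7 the either-direction rate is about 4 to 6 times 5% (19/5 = 3.8; 30/5 = 6). The favourable rate is about 4 to 6 times 2.5% (10/2.5 = 4; 15/2.5 = 6).

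These figures cover the eight ITT comparisons only. Counting the PP repeats as well can only raise them. By how much is not quantified, and the two sets overlap heavily.

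**Cost of adjusting across all eight.** The first step of Holm, like Bonferroni, is 0.05/8 = 0.00625.
- Power for an assumed difference of 0.8 SD falls from 72% to 42%.
- The difference detectable with 80% power is (z for the level + z for the power) × √(1/15 + 1/30). At 0.05 it is (1.960 + 0.842) × 0.316 = 0.89 SD. At 0.00625 it is (2.734 + 0.842) × 0.316 = 1.13 SD.

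**The case against.** The best defence is that this is a pilot, and says so in the title, Objectives, Sample size and Discussion. Finding a primary endpoint for the later trial is a stated objective, which explains why several candidates are carried and none leads. The Discussion reserves confirmation for a full-scale RCT. In endpoint screening, strict family-wise control is partly a matter of judgement. This stands, and it lowers the severity. It does not remove the point: efficacy is part of the primary objective, the tests are not labelled exploratory, and the abstract's wording conflicts with the main Discussion.

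Four stronger readings are tempting, and the article does not support them.
- *The lipid outcomes lie outside the hypothesis.* They do not. The Hypothesis section expects them to improve, and the Discussion gives a preclinical reason for including them.
- *The article lets any one outcome prove efficacy.* No sentence says so. The article sets a per-test level and is silent on how the eight results combine, so the rates above are conditional on that reading.
- *The false-positive rate is 34%.* That needs independence and counts results in either direction, including against PURIAM110. The favourable-direction rate is about half, and at a correlation of 0.9 it is only 6%.
- *The trial is confirmatory by design.* One word in the abstract points that way, in a sentence that goes on to further RCTs. The main Discussion says the opposite.

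**Conclusion.** The point holds in a limited form. Eight unranked primary outcomes, each called significant at an unadjusted two-sided 5% in two analysis sets, do not keep the overall error at 5% if any one result is taken as efficacy. On that reading, with no true effect, at least one of the eight ITT tests is significant in about 19% to 30% of trials at correlations of 0.7 to 0.3 (12% at 0.9, 34% if independent). At least one favours PURIAM110 in about 10% to 15%, against 2.5% for a single test. The size depends on assumed correlations and on the reading rule; that the rate exceeds the single-test level holds across the whole range examined.

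Separately, the abstract and the main Discussion disagree on whether the trial confirms efficacy, and they need to be reconciled. Given the pilot purpose, this is a should-fix, not a defect that invalidates the trial.

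**What to change.** Before unblinding, do one of the following.

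1. Name one lead outcome and test it in ITT at two-sided 5%. Change in fasting glucose from visit 2 to visit 4 is one reasonable choice, but not the only one, since the hypothesis also covers lipids and does not choose among glucose measures.
2. Label all eight as exploratory candidates for the later RCT's endpoint, with no significance claims.

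In either case, report the remaining outcomes and all PP results as between-group differences with 95% confidence intervals and no significance claims. In the abstract, replace the promise to confirm efficacy and safety with one to estimate them.

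The cost is a few wording changes, and fewer outcomes can be called significant. Holm across all eight would control the error but is not recommended here, because it takes too much power with 30 vs 15.

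The Study design section dates the study from December 2006. If the data are already unblinded, a lead outcome can no longer be pre-specified, and only the exploratory label and the interval reporting remain.
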